### Recruitment

A total of 60 participants who meet the eligible criteria will be competitively recruited from three sites of university-affiliated Korean medicine teaching hospitals. Patient recruitment will be advertised by using posters and institution website bulletin boards in trial hospitals or local community newspaper advertisements.

### Interventions

On enrollment in the study, participants will be randomly assigned to the OJS and placebo groups. Each will be administered either 3 g of OJS or the placebo drug (granulated extract) three times a day orally for 8 weeks.

OJS contains *Atractylodis Rhizoma* 44.3 mg, *Ephedrae Herba* 22.3 mg, *Citri Reticulatae Pericarpium* 22.3 mg, *Pinelliae Rhizoma* 22.3 mg, *Zingiber officinale** Rosc*. 22.3 mg, *Cinnamomi Ramulus* 22.3 mg, *Angelicae Gigantis Radix* 22.3 mg, *Jujubae Fructus* 22.3 mg, *Radix Glycyrrhizae* 22.3 mg, *Paeoniae Radix Alba* 22.3 mg, *Angelicae Dahuricae Radix* 22.3 mg, *Poria (Hoelen)* 22.3 mg, *Aaurantii Immaturus Fructus* 22.3 mg, *Cnidii Rhizoma* 22.3 mg, *Magnoliae Cortex* 22.3 mg, *Platycodi Radix* 22.3 mg, and *Cyperi Rhizoma* 13.3 mg. The placebo drug will be prepared identically in all respects to the active oral drug without active ingredients, containing lactose 1.7 g, corn starch 0.1 g, citric acid, 0.1 g, OJS herbal flavor 0.1 g, and caramel food coloring 0.1 g.

Both IP will be manufactured by Hanpoong Pharm and Foods Co., Ltd. (Jeonju, Korea). The daily dosage of OJS in this trial is determined based on the information from product approval certification by the Korean Ministry of Food and Drug Safety (MFDS).

During the study period, only study IP is allowed to use. If participants are willing to administer the drugs other than IP, they should notify the site investigator prior to administration and confirm whether it is available or not.

### Outcomes

All of the assessments will be performed by the trained investigators in each site. Before initiating the trial, all of the investigators will participate in the trial SOP training for being thoroughly familiar with the trial process and outcome assessments.

#### Primary outcome variable

##### Visual Analog Scale (VAS)

The mean changes of VAS score from baseline will be assessed the severity of CHHF symptoms by using a VAS [15, 16]. It is a 10-point scale ranging from 0 (no coldness) to 10 (most severe coldness). Patients will be asked to mark on the line at a point that represents the severity of the CHHF at every visit. The higher points represent greater severity of CHHF.

#### Secondary outcome variables

The secondary outcomes include the mean changes in body skin temperature at particular acupoints, total score of the Korean version of the WHO Quality of Life-BREF.

##### Body skin temperature

The enrolled participants will be advised to avoid consuming caffeine, alcohol, tobacco, undergoing vigorous exercise, and taking hot showers for at least 2 h before clinic visit. After arrival at the clinic, the CRC seats the participants in the examination room (24 ± 1 °C) for at least 20 min for relaxation. Body skin temperature (BT) will be measured at specific acupoints of the body which are distributed on the extremities: center of both palms (PC9), anterior upper arms (LU4), thighs (ST32), and junctions of the first and second metatarsal bones (LR3) by using a thermometer (Testo 835-T1, Lenzkirch, Germany) at each visit [17]. The differences between each acupoint and two points on each of the upper and lower extremities from baseline will be calculated to evaluate the change of body temperature.

##### Cold stress test

The cold stress test (CST) is generally used to assess the severity of cold sensitivity in patients with vascular disorders [18]. For performing the procedure, the participants will rest for 20 min in the examination room (24 ± 1 °C) and then immerse both hands into a container of iced water (20 °C) for 30 s. The BTs of both palms (PC8) are assessed by using an infrared thermometer (Testo 835-T1, Lenzkirch, Germany), pre and post immersion and 6 min post immersion. The CST will be performed at visits 2 and 5. The recovery rate (RR) equation of the CST is as follows:$$ RR=\left({T}_6-{T}_0\right)/\left({T}_{\mathrm{base}}-{T}_0\right)\times 100\%, $$

where: *T*_base_: the skin temperature of PC8 at pre immersion

*T*_0_: the skin temperature of PC8 measured at post immersion

*T*_6_: the skin temperature of PC8 measured at 6 min post immersion

The higher RR represents faster recovery to normal temperature. The mean change of RR from baseline will be calculated to evaluate the efficacy of OJS.

##### Korean version of the WHO Quality of Life-BREF

The mean changes of the WHO Quality of Life abbreviated version (WHOQOL-BREF) score from baseline will be assessed the quality of life of patients with CHHF symptoms. The WHOQOL-BREF is an effective, cross-culturally comparable, quality of life questionnaire. It consists of 26 items with five domains: general quality of life (2), physical health (7), psychological health (6), social relationships (3), and environmental health (8). To estimate quality of life scores in the Korean population, the Korean version of WHOQOL-BREF by Min et al. [19], will be used and measured at visits 2 and 4. Raw scores in each domain will be converted into a 0–100 transformed score where a higher score indicates better quality of life.

### Safety assessment

For safety assessment, we will perform the general physical examination and vital sign measurement at every visit. The kidney and liver function tests (measurement of blood urea nitrogen (BUN), creatinine (Cr), ALT, AST, and γ-GT levels) will be conducted at the screening visit and visit 4.

### Adverse event (AE) reporting

All participants will voluntarily report occurrences of AEs during trial at every visit. If there is an AE, the site investigator will immediately report to the sponsor any serious AE, whether or not considered drug related, and also report to the site Institutional Review Boards (IRB). After receiving an AE report, the site principal investigator (PI) decides whether to withdraw from or continue to participate in the trial. The collected AEs must be recorded in the CRF by the site investigator.

### Statistical analysis

An independent statistics expert will perform the statistical analysis in a blind manner. Intention-to-treat (ITT) analysis will be the main analysis for efficacy assessment for use in all participants who receive at least one dose of any IP; in addition, per-protocol (PP) analysis will be performed in participants who complete the trial except dropouts. Missing data will be adjusted using the last-observation-carried-forward (LOCF) imputation method. The statistical level of significance will be set at *P* < 0.05. All statistical analyses will be performed using SPSS, version 25.0. (IBM Inc., Chicago, IL, USA).

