### Sample size calculation

Sample size will be not calculated because of the lack of research on the use of OJS in the treatment of patients with CHHF and pilot clinical trial for OJS. Considering visit frequency of CHHF patients and availability of workforce at each site, a total of 60 participants, 30 per group will be included.

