### Efficacy

The primary endpoint is the mean change in VAS score between the OJS group and the placebo group from baseline to V5; the secondary endpoints are the mean changes from baseline at V5 in BT, WHOQOL-BREF, and CST. Both assessments will be analyzed using chi-square or Fisher’s exact tests for categorical data and Student’s *t* tests or Mann-Whitney *U* tests for continuous data. Additionally, the repeated measures analysis of variance (ANOVA) will be performed to assess the presence of any significant differences in the mean VAS, BT, and WHOQOL-BREF scores between groups at different time points (each visit after baseline assessment).

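### Last observation carried forward is the only stated missing-data method for the main analysis; it can shift the week-8 VAS effect in either direction and scores the cold stress test change as zero for anyone who leaves before the second test

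*Protocol article*

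**What the plan says.** The missing-data rule is one sentence in the Statistical analysis section: "Missing data will be adjusted using the last-observation-carried-forward (LOCF) imputation method". It is not restricted to particular outcomes, visits or reasons for missingness. The same section states "Intention-to-treat (ITT) analysis will be the main analysis for efficacy assessment for use in all participants who receive at least one dose of any IP", so dosed participants who drop out enter the main analysis with filled-in values. The only other analysis set is secondary: "per-protocol (PP) analysis will be performed in participants who complete the trial except dropouts".

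The Efficacy section compares changes from baseline by t test or Mann-Whitney test and adds that "the repeated measures analysis of variance (ANOVA) will be performed to assess the presence of any significant differences" in mean VAS, skin temperature and quality of life across visits.

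The schedule (Table 1) places VAS at screening, D1, D28, D56 and D84, so D28 is the only post-baseline value before week 8. The cold stress test appears twice in Table 1, at visit 2 and visit 4 (D56). The Cold stress test section says visits 2 and 5.

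The Withdrawals section takes participants out for serious adverse events, compliance below 70%, use of forbidden medication and other reasons, and keeps them in the intention-to-treat analysis. On planning assumptions, the Sample size section says "Sample size will be not calculated because of the lack of research on the use of OJS". It fixes 30 per group on practical grounds and gives no effect size, SD or dropout rate.

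**The concern.** LOCF treats a participant's score as frozen from the last visit onward. A dosed participant who leaves before D28 is scored as having no change at week 8. One who leaves after D28 keeps the D28 value. If symptoms are still moving, both scores are wrong on average. The error cancels between arms only when the dropout pattern is the same in both and there is no treatment effect.

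Unequal dropout is plausible here, because several withdrawal criteria (adverse events, poor compliance) may occur more often in one arm. The filled values also enter the test as if they had been observed, which distorts the standard deviation.

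The trial's stated purpose is to inform a larger confirmatory trial. A shifted effect and a distorted SD would pass straight into that design.

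**Working it through.** The article states no bias, power, SD or dropout figure, so there is nothing to reproduce. The check uses the visit schedule and assumed inputs.

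**Inputs from the article.** 30 per group; VAS at D1, D28 and D56; significance level 0.05 (two-sided assumed); two cold stress tests.

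**Assumed inputs.** Placebo improves by 1 point at D28 and 2 points at D56. SD is 1.5 at each visit, with correlations 0.5 (D1 with D28), 0.5 (D1 with D56) and 0.6 (D28 with D56). Dropout is random within arm, and half of dropouts leave before D28. A true effect of -1.0 at D56 is taken as -0.5 at D28. Dropout is written OJS/placebo.

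**Expected LOCF change in one arm** with dropout d:

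(1 - d) × m56 + d × 0.5 × m28 + d × 0.5 × 0

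- Placebo, and OJS under no effect (m28 = -1, m56 = -2): -2 + 1.5d.
- OJS with the true effect (m28 = -1.5, m56 = -3): -3 + 2.25d.

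**Difference, OJS minus placebo:**

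| Truth | Dropout | OJS | Placebo | LOCF difference |
|---|---|---|---|---|
| 0 | 20%/20% | -1.70 | -1.70 | 0 |
| 0 | 20%/10% | -1.70 | -1.85 | +0.15 |
| 0 | 30%/10% | -1.55 | -1.85 | +0.30 |
| -1.0 | 20%/20% | -2.55 | -1.70 | -0.85 |
| -1.0 | 20%/10% | -2.55 | -1.85 | -0.70 |
| -1.0 | 10%/30% | -2.775 | -1.55 | -1.225 |

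**Simulation under the same inputs** (6,000 to 20,000 runs, t test on change):

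- No effect, 20%/20%: type I error about 5% with LOCF.
- No effect, 20%/10%: 6.5% to 6.7%.
- No effect, 30%/10%: 11% to 12% with LOCF, about 5% on observed week-8 data.
- True -1.0, 20%/10%: power about 37% with LOCF, 63% on observed data.
- True -1.0, 20%/20%: about 51% with LOCF, 62% on observed data.

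Observed week-8 data averaged about -1.0 in every scenario with a true -1.0. With SD of change 2 instead of 1.5, type I error at 30%/10% is 9.0% with LOCF and 5.1% on observed data: the same direction, smaller in size.

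**Cold stress test.** There is one post-baseline test on either reading of the visit number. If baseline is carried forward, the recovery-rate change is exactly 0 for a participant without that test, so the expected difference is (1 - dOJS) × mOJS - (1 - dplacebo) × mplacebo. With assumed changes of 20 and 10 points (true difference 10):

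- 20%/20%: 0.8 × 20 - 0.8 × 10 = 8.0.
- 20%/10%: 0.8 × 20 - 0.9 × 10 = 7.0.
- 30%/10%: 0.7 × 20 - 0.9 × 10 = 5.0.

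The zeros also shrink the SD. For mean change 15 and SD 30, the variance at dropout d is (1 - d)(30² + 15²) - ((1 - d) × 15)². That gives an SD of 28.8 at 10% dropout, 27.5 at 20% and 26.0 at 30%.

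**The case against.** The strongest reply is that the article already plans a completer analysis. Under the random dropout assumed above, that analysis is unbiased: at a true -1.0 with 20%/10% dropout, completers average about -0.995 against -0.70 for LOCF. A gap between the two planned analyses would therefore expose the problem. This stands as far as it goes. But the completer analysis is secondary, and it has no protection if dropout depends on earlier outcomes.

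Second, the sizes are modest unless dropout is markedly unequal. At 20%/10% with no effect, the bias of 0.15 is less than half the sampling SD of the difference (about 0.40). At 5%/5% a true -1.0 averages -0.96. This also stands. The 30%/10% case means 9 against 3 dropouts of 30.

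Third, several stronger readings go beyond the document:

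- A reader might infer that the trial itself expects VAS to move in both arms. The article gives no trajectory and no placebo response.
- A reader might infer bias whenever dropout differs between arms. If mean VAS is flat after the last observed visit, unequal random dropout does no harm.
- A reader might infer that every dropout's cold stress change becomes zero. Under Table 1, someone lost between D56 and D84 already has the second test. The zero also presumes that baseline counts as an observation to carry, which is the natural reading for an all-dosed set but is not spelled out.
- That the repeated measures ANOVA runs on filled data is likewise the natural reading, not an explicit statement.
- A likelihood-based estimator that conditions on baseline has RMSE 0.37 against 0.51 for LOCF (true -1.0, 20%/10%). That gain is not all due to missing-data handling: the unadjusted observed-data difference has RMSE 0.42.

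**Conclusion.** The concern holds in limited form. The protocol fixes LOCF as its only stated missing-data rule for the main analysis. This is a stated choice, and an analysis plan that merely added sensitivity analyses would not change it. The choice is poor because the direction of its bias is not controlled: towards zero under equal dropout with a growing effect, either way under unequal dropout, and none under equal dropout with no effect. It therefore cannot be defended as conservative.

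Under the assumed inputs, the shift in the primary estimate is roughly 0.15 to 0.30 points, and type I error reaches 11% to 12% only at the 30%/10% extreme. These figures show a mechanism. They do not predict this trial, because every trajectory, SD and dropout rate behind them is assumed. The zero for participants without a second cold stress test follows from the schedule alone, once baseline is carried forward.

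Confidence is high on the principle and low on any particular size. In a 60-participant pilot without a power calculation, this is something the sponsor should change, mainly because the estimates are meant to feed the next trial.

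**What to change.** 1. Reconcile the labels first. Week 8 is visit 4 (D56) in Table 1, but the Efficacy and Cold stress test sections refer to visit 5. If that meant D84, LOCF would also carry week-8 values into the off-treatment follow-up. The WHOQOL-BREF section gives visits 2 and 4, while Table 1 shows visits 2, 3, 4 and follow-up.
2. Make the primary analysis a mixed model for repeated measures on observed post-baseline VAS, with treatment, visit, treatment-by-visit, visit-2 VAS and hospital (the stratification factor), unstructured covariance, and the week-8 treatment contrast as the primary estimate. This replaces both LOCF and the repeated measures ANOVA.
3. Use the same model for skin temperature and, if it proves to be measured at more than one post-baseline visit, for WHOQOL-BREF.
4. Analyse the cold stress test by ANCOVA on observed data, adjusted for baseline recovery rate.
5. Keep LOCF only as a sensitivity analysis.

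The cost is wording in the protocol and analysis plan and slightly more analysis work; the named SPSS package has a mixed-model procedure. No visit or procedure changes, and the article reports enrollment as ongoing. The downside is reliance on a missing-at-random assumption, which should be stated.

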### General characteristics

Descriptive statistics are used to summarize the study populations and safety data. For the purposes of this analysis, descriptive statistics refers to the sample size (*N*), mean, and standard deviation for any group variable.

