1. Those taking calcium antagonists or beta-blockers for the purpose of treating CHHF 2. Those with one or more ulcers or gangrene of the finger 3. Those who have been diagnosed with hypothyroidism or are taking thyroid-related medication 4. Those who are diagnosed with an autoimmune disease 5. Those who are diagnosed with carpal tunnel syndrome or have a positive result in Tinel and Phalen’s tests 6. Those who have been diagnosed with cervical disk herniation 7. Those who have been diagnosed with diabetes 8. Those who are currently medicated with drugs that may affect CHHF symptoms, such as anticoagulants 9. Those who have serious liver dysfunction (AST and ALT, each 100 IU/L or more) or renal dysfunction (creatinine (Cr) 2.0 mg/dL or more) 10. Those who do not (cannot) comply with treatment and follow-up due to mental illness such as behavior disorder, depression, anxiety neurosis, schizophrenia, or serious mental illness 11. Those who are diagnosed with moderate anemia and hematologic disorders (adult non-pregnant women hemoglobin (Hb) level less than 7 g/dL, hematocrit (Hct) level less than 26%, white blood cell (WBC) level 11,000/mm^3^ or more) 12. Those with systolic blood pressure (SBP) 180 mmHg or diastolic blood pressure (DBP) greater than 100 mmHg based on average value of at least 2 measurements 13. Those who have suspected arrhythmia requiring treatment on EKG, or have been diagnosed with heart diseases, such as, ischemic heart disease and so on 14. Those who are addicted to alcohol or drugs 15. Fertile women who are pregnant (positive urine-HCG), have a pregnancy plan, or do not agree to the appropriate method of contraception 16, Those who have been diagnosed with a malignant tumor 17. Those who are currently participating in other clinical trials 18. Those who are unable to understand and speak Korean 19. Those who are judged to be inappropriate for the clinical study by the researchers	

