### Safety

Safety variables will be assessed based on the frequency and severity of treatment-emergent AEs as well as changes in vital signs and laboratory parameters. Vital signs and laboratory measurements will be summarized descriptively by treatment group using both observed values and change from baseline values.

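### N, mean and SD, the stated summary for laboratory and vital-sign safety data, do not show how many women had a marked rise; ranges and counts by arm would (minor)

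*Protocol article*

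**What the plan says.** The General characteristics section of the protocol article states: "Descriptive statistics are used to summarize the study populations and safety data". Its next sentence defines these statistics as the sample size, "mean, and standard deviation for any group variable". The Safety section under the statistical methods adds: "Vital signs and laboratory measurements will be summarized descriptively by treatment group using both observed values and change from baseline values". Read together, the stated summary for ALT, AST, γ-GT, BUN, creatinine and blood pressure is N, mean and SD by arm, for observed values and for changes.

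Adverse events are handled separately, through the "frequency and severity of treatment-emergent AEs". On collection, the Adverse event reporting section says: "All participants will voluntarily report occurrences of AEs during trial at every visit". Table 1 also schedules an adverse event check-up at visits 3 and 4 and at FU1. Vital signs are taken at every visit. The kidney and liver tests "will be conducted at the screening visit and visit 4", so there is one on-treatment laboratory measurement.

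Numerical limits for these variables appear only among the exclusion criteria in Table 2: "Those who have serious liver dysfunction (AST and ALT, each 100 IU/L or more) or renal dysfunction (creatinine (Cr) 2.0 mg/dL or more", and for blood pressure a systolic value of 180 mmHg or "diastolic blood pressure (DBP) greater than 100 mmHg based on average value of at least 2 measurements".

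**The concern.** Laboratory and blood-pressure safety signals usually lie in a few individuals, not in a shift of the whole group. A mean dilutes one or two large rises. An SD reacts to them, but does not say whether the cause is one extreme woman or broader scatter across several.

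Safety is a stated aim, and the Discussion says that the pilot should inform a confirmatory trial. Anyone planning that trial needs to know whether 0, 1 or 2 of about 30 treated women had a marked rise. The laboratory and vital-sign table, as described, does not tell them. Such a case would be counted only if it were also recorded as an adverse event. The article gives no rule for when a value, as opposed to a symptom, becomes one.

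**Working it through.** **Scope.** The definition cannot apply to categorical data, and adverse events are counted separately. The check therefore covers continuous laboratory and blood-pressure values only. The plan has no figure of its own to reproduce here.

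**Inputs.** From the Sample size calculation section: n = 30 per arm. Assumed, because the article gives no such values: SD of change s = 8 to 15 IU/L for ALT, 0.10 mg/dL for creatinine and 10 mmHg for systolic pressure (SBP), with placebo keeping these SDs and a mean change of 0.

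**Step 1: effect on mean and SD.** Let k women rise by an extra d, unrelated to the background scatter.

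- Mean shift = k·d/n
- SD after = √(s² + d²·k(n−k)/(n(n−1)))
- Ratio = SD after divided by s. The square of the ratio is compared with F on 29 and 29 df (two-sided). Its 97.5% point is 2.10, a ratio of 1.45. With outliers present this is a yardstick, not an exact test.

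| Case | Mean shift | SD after | Ratio | p |
|---|---|---|---|---|
| ALT +100, k=1, s=8 | 100/30 = 3.3 | √(64+333.3) = 19.9 | 2.5 | <0.001 |
| ALT +100, k=1, s=15 | 3.3 | √(225+333.3) = 23.6 | 1.6 | 0.017 |
| Creatinine +1.3, k=1 | 1.3/30 = 0.04 | √(0.01+0.0563) = 0.26 | 2.6 | <0.001 |
| SBP +40, k=2 | 80/30 = 2.7 | √(100+103.0) = 14.2 | 1.42 | 0.06 |
| SBP +40, k=1 | 40/30 = 1.3 | 12.4 | 1.24 | 0.26 |

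So the SD would draw attention for ALT and creatinine, but not reliably for SBP.

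**Step 2: can the count be recovered from all the rows together?** Sets of 30 baseline and 30 visit 4 values were searched for that reproduce the baseline, visit 4 and change rows (mean and SD) while differing in the number of women at or above the entry limit. For ALT, baseline was held to 5–60 IU/L and visit 4 to at least 5 IU/L.

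- ALT baseline 20.0 (8.0), visit 4 23.3 (19.9), change +3.3 (19.9): fits 0 women at 100 or more (one solution has a highest value of 71) or 1 woman (highest about 118). Two is impossible: two women at 100 leave the other 28 with a mean of (700 − 200)/28 = 17.86, so the visit 4 SD is at least √(82.14²·56/870) = 20.8.
- ALT baseline 25.0 (15.0), visit 4 28.3 (23.6), change +3.3 (23.6): fits 0, 1 or 2 women. Three would need an SD of at least √(79.63²·81/870) = 24.3.
- Creatinine baseline 0.70 (0.10), visit 4 0.743 (0.258), change +0.043 (0.258): fits 0 or 1 woman at 2.0 mg/dL or more.

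**Step 3: what a count would add.** Exact (Clopper–Pearson) 95% intervals: 0/30, 0% to 11.6%; 1/30 = 3.3%, 0.1% to 17.2%; 2/30 = 6.7%, 0.8% to 22.1%.

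**The case against.** The strongest objection is that this is an omission and not an error. The definition does not say that nothing else will be shown, it stands in a condensed article, and ranges, abnormality counts and listings are usually left to an analysis plan. Part of this stands: nothing in the text forbids further summaries. But the article does more than stay silent. It names safety data, defines the summary and then applies it. A team following the text would produce a table without counts.

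Four narrower objections also stand.

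- Adverse-event capture does not rest on voluntary reports alone. Table 1 schedules check-ups at visits 3, 4 and FU1, and the investigator must record collected events in the case report form.
- The loss of the count is not caused by having 30 women per arm. Mean and SD do not determine a count at any N.
- The wider SD would probably prompt a look at the raw ALT and creatinine values.
- A count at 180 mmHg alone would miss rises such as 120 to 160 mmHg, so a remedy based only on the entry limits would be incomplete for blood pressure.

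A reader might infer that marked rises would go unrecorded, or that the plan conceals harm. The documents do not support that. The values are collected, and an investigator may enter a rise as an adverse event. What is missing is a statement of when a laboratory or blood-pressure value counts as one.

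**Conclusion.** The point holds as a minor, cheap improvement to safety reporting. The stated summary of continuous laboratory and vital-sign data does not show how many women had a marked rise. A widened SD may hint at one for ALT or creatinine without giving the number. For blood pressure it may not stand out at all. Adverse-event reporting is a partial safeguard.

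The sizes of the shifts and SD ratios depend on the assumed SDs and rises. The conclusion that N, mean and SD do not fix the count does not. No endpoint, sample size, randomisation or efficacy conclusion is affected.

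**What to change.** Keep mean and SD. Add to the Safety section, by arm:

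1. Median, minimum, maximum and largest individual rise from baseline for ALT, AST, γ-GT, BUN, creatinine, SBP and DBP. This is the only item that covers γ-GT and BUN, for which Table 2 gives no limit.
2. Number and percentage, with exact 95% CI, of women newly reaching AST or ALT of 100 IU/L or more, or creatinine of 2.0 mg/dL or more, at visit 4; and SBP of 180 mmHg or more, or DBP above 100 mmHg, at visits 3, 4 and FU1. The denominator is treated women with an observed value at that visit. Label these as reporting thresholds adapted from the entry criteria, not as on-treatment limits. The entry criterion joins AST and ALT with 'and', and averages at least two blood-pressure readings.
3. For blood pressure, the number of women whose rise from baseline exceeds a size fixed before unblinding, so that a rise from 120 to 160 mmHg is counted.

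The cost is one extra table and a few sentences, from data already collected, with no new visits or tests. The downsides are wide intervals with about 30 women per arm and a safety statement that may look less favourable.
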